#### 2.5.3 Sample size

In this study, HAMD-17 is used as the leading indicator for sample size calculation. Based on the results in the preliminary clinical study, i.e., observation of the Hamilton Depression Scale score reduction (ΔHAMD) results of 6.13 ± 1.96 Mean ± SD reduction in the test group and 4.57 ± 1.87 reduction in the control group, according to the sample size calculation formula.

$$\frac{2\;(Z_{\alpha /2}+Z_{\beta }{)}^{2}\times \sigma^{2}}{\delta^{2}}$$

α = 0.05, 1-β = 0.9, σ = 1.96, δ = (6.13–4.57) = 1.56

α is set to 0.05, the statistical power is set to 0.9, and a two-sided test is conducted. Based on the calculated dropout rate of 20%, each group will eventually require 42 patients; that is, a total of 84 participants will be randomly divided into two groups in a 1:1 ratio.

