### 2.6 Outcome measures

The results cover three indicators: scale indicators, serum indicators and serum metabolomics. Scale assessments will be performed at baseline, week 2 and week 4. Serum indicators and serum metabolomics will be tested at baseline and week 4. All assessments will be performed by researchers who are blinded to treatment assignment.

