### 2.9 Statistical analysis

Third-party statisticians who are not engaged in the allocation process or trial implementation will be invited to conduct statistical analysis and participate in the whole process, including trial design, implementation, and data analysis. Outcome measures at baseline and two-time points after the intervention will be analyzed to assess treatment effectiveness. Data will be analyzed using SPSS26.0 software according to the intention-to-treat principle of data analysis. Subgroup analysis will be performed if data for different clinical features are available. Chi-square tests will be used to assess sample characteristics and gender. Continuous variables will be summarized as mean ± standard deviation (SD). Continuous variables will be compared by the Student t-test or Wilcoxon rank sum test, and categorical variables will be reached by the Pearson chi-square test or Wilcoxon rank sum test reported by percentage. Data conforming to the normal distribution will be analyzed by one-way analysis of variance. The comparison of each group will be analyzed by T-test. A non-parametric rank sum test and the Mann-Whitney U test will be used to assess measurement data that does not have a normal distribution or homogeneous variance. A bilateral 5% significance level will be used, and the corresponding 95% confidence interval will be calculated as far as possible. P-value <0.05 would be set as the significance level, and the difference would be considered statistically significant.

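### Section 2.9 fixes unadjusted two-group tests with a variance-driven switch to Mann-Whitney, and does not say whether the HAMD-17 reduction used for the sample size is what will be tested

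*Protocol article*

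**What the plan says.** On visits, section 2.6 states: "Scale assessments will be performed at baseline, week 2 and week 4". Table 1 shows this for HAMD-17, SDS, NIHSS and MBI. Serum markers are taken at baseline and week 4.

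On sample size, section 2.5.3 works with the fall in HAMD-17: "observation of the Hamilton Depression Scale score reduction (ΔHAMD) results of 6.13 ± 1.96 Mean ± SD reduction in the test group". For the comparator it gives "4.57 ± 1.87 reduction in the control group". The inputs are "α = 0.05, 1-β = 0.9, σ = 1.96, δ = (6.13–4.57) = 1.56", and the result after 20% dropout is 42 per arm, 84 in total.

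On analysis, section 2.9 says that baseline and two later time points will be analysed. It names the Student t-test or the Wilcoxon rank sum test for continuous variables, and then: "Data conforming to the normal distribution will be analyzed by one-way analysis of variance. The comparison of each group will be analyzed by T-test". The rank test (Mann-Whitney U) "will be used to assess measurement data that does not have a normal distribution or homogeneous variance". The level is given as: "A bilateral 5% significance level will be used". The section names no baseline covariate and no model that links the visits. It does not say whether the score at a visit or the change from baseline is compared.

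**The concern.** There are four linked weaknesses in what section 2.9 states.

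- **Tested quantity.** The sample size rests on the SD of a change score, but the analysis section does not say that change is tested. The planned power holds for change. It may not hold for raw week-4 scores.
- **Baseline and visits.** Baseline HAMD-17 is collected on everyone and is likely to predict week 4. Using it as a covariate narrows the interval at no cost. A week-4 t-test also cannot use the week-2 score of a patient who leaves later, although 20% dropout is expected and intention-to-treat is claimed.
- **One-way ANOVA.** With two arms it is the t-test again. If it were run across visits, it would treat one patient's repeated scores as independent.
- **The switch.** Mann-Whitney does not test equality of means when spreads differ, so it does not repair unequal variances. Choosing the test from the data also changes the quantity being compared. The rule covers every continuous outcome, including the serum markers, where skew and unequal spread are plausible.

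**Working it through.** **Inputs.** From section 2.5.3: two-sided α 0.05, power 0.90, σ = 1.96, δ = 6.13 − 4.57 = 1.56, arm SDs 1.96 and 1.87, dropout 20%. The article gives no baseline-to-week-4 correlation r, so r is assumed to be 0.5 to 0.8, with equal variances at the two visits. The SD ratios and skewed shapes in step 5 are also assumptions.

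**1. The plan's own figure.** n = 2(1.960 + 1.282)² × 1.96² / 1.56² = 33.17 per arm. Dividing by 0.8 gives 41.47, rounded up to 42, so the stated 42 per arm reproduces. (Rounding up to 34 before dividing gives 42.5, so 43.)

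**2. t-test on the reduction.** With 34 evaluable per arm and SD 1.96, the power is 0.90, as planned.

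**3. Baseline-adjusted and raw-score analyses.** With equal variances at both visits, the SD of the week-4 score is 1.96 / √(2(1 − r)). The ANCOVA residual SD is 1.96 × √((1 + r)/2), so the variance relative to the change score is (1 + r)/2. t-test power at 34 per arm:

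| r | ANCOVA SD | Power, ANCOVA | Week-4 SD | Power, raw week 4 |
|---|---|---|---|---|
| 0.5 | 1.70 | 0.96 | 1.96 | 0.90 |
| 0.6 | 1.75 | 0.95 | 2.19 | 0.82 |
| 0.7 | 1.81 | 0.94 | 2.53 | 0.71 |
| 0.8 | 1.86 | 0.93 | 3.10 | 0.53 (see objection) |

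The variance saving against change scores is 25% at r = 0.5 and 10% at r = 0.8.

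**4. One-way ANOVA.** On two simulated groups its p-value equals that of the t-test (0.8628 for both). If it were run over the three visits as though they were independent, with 34 patients, its true level would be 1.6%, 0.4% and 0.02% at within-patient correlations of 0.3, 0.5 and 0.7. Its power for a shift of 0.4 SD at correlation 0.5 would be 0.18, against 0.53 for repeated-measures ANOVA.

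**5. The switch.** Rejection rates at nominal 5% with equal means, by simulation:

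| Data | SD ratio | n per arm | Mann-Whitney | Welch |
|---|---|---|---|---|
| Normal | 1.96 : 1.87 | 34 | 5.2% | 5.1% |
| Normal | 2 : 1 | 34 | 5.9% | 4.9% |
| Normal | 3 : 1 | 34 | 6.7% | 5.0% |
| Gamma, shape 8 (mild skew) | 2 : 1 | 42 | 8–9% | 5% |
| Gamma, shape 4 | 2 : 1 | 42 | 11–12% | 5% |
| Gamma, shape 2 (moderate skew) | 2 : 1 | 42 | 18% | 5% |
| Exponential | 2 : 1 | 42 | 34% | 5–6% |
| Exponential | 1.96 : 1.87 | 42 | 5% | 5% |

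The full switch was also run at 34 per arm with Shapiro and Levene pre-tests (an assumption, as the article names none). With normal data and the protocol's SDs it rejects 5.4% of the time under no difference. Its power is 0.906, against 0.909 for the t-test alone.

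**The case against.** The strongest reply is that much of this concerns efficiency rather than error, and that an unseen analysis plan may fill the gaps.

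- **Baseline is not ignored.** A reader might infer that it is. The documents do not support that: section 2.5.3 is built on the HAMD-17 reduction, section 2.6.1 builds the effective rate on percentage reduction from baseline, and section 2.1 includes change in the primary outcome. Baseline enters by subtraction. What stands is that section 2.9 does not name the tested quantity and does not adjust for baseline.
- **The trial is not shown to be underpowered.** A t-test on the reduction is valid under randomisation and reaches its 90%. The gain from ANCOVA is an improvement on a sound test. A shortfall needs raw week-4 scores and r above about 0.5.
- **The 0.53 figure should not be relied on.** At r = 0.8 it implies a baseline SD of 1.96/√0.4 = 3.10. Section 2.2.1 restricts entry to HAMD 8 to 17, and even a uniform spread over those ten scores has SD √(99/12) = 2.87. The 2.53 implied at r = 0.7 is possible but wide.
- **The 34% rate is an extreme case.** It needs exponential skew and a 2:1 SD ratio together. Strictly, it is also a change of hypothesis, since Mann-Whitney does not claim to test means.
- **ANOVA across visits is only one reading.** Section 2.9 does not state it. Between two arms the ANOVA is redundant, not invalid.

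The appeal to an unseen analysis plan does not remove the core. Covariates and model details may be left to such a plan, but the unadjusted tests, the ANOVA and the rank test for unequal variances are methods that the article itself states.

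**Conclusion.** The point holds in a limited form. Section 2.9 states a redundant ANOVA, uses a rank test as the remedy for unequal variances, and leaves the tested quantity unconnected to the one that was powered. Provided the reduction is tested, power stays at 0.90. Adjusting for baseline would raise it to about 0.96 to 0.93, given assumed correlations of 0.5 to 0.8 and equal variances at both visits. Under the same assumptions, a raw week-4 test would have power 0.82 at correlation 0.6 and 0.71 at 0.7.

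The harm from the switch depends on the data: about 5% rejection at the protocol's own HAMD-17 SDs, and about 9–18% with a 2:1 SD ratio and mild to moderate skew. It would be wrong to conclude that the primary analysis is invalid or that error rates will be inflated. The documents show neither, and give no correlation, skew or serum-marker SD from which to judge. The change should be made because it is free and removes choices that would otherwise be made after seeing the data.

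**What to change.** - **Primary analysis.** Make it the between-arm difference in HAMD-17 at week 4, adjusted for baseline HAMD-17, in all randomised patients, with a 95% confidence interval. Use either ANCOVA at week 4 or a mixed model for weeks 2 and 4 with treatment, visit, treatment-by-visit and baseline. State which one.
- **Other outcomes.** Use the same form for SDS, NIHSS and MBI, and baseline-adjusted ANCOVA for the serum markers, on the log scale if skewed.
- **Delete** the one-way ANOVA and the switch driven by normality or variance. Handle unequal variances with Welch or robust standard errors, and keep the rank test as a sensitivity analysis.

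The cost is protocol wording and a little analysis work. The planned SPSS 26 can fit these models, and no new data, visits or patients are needed. The sample size of 84 can stay.

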#### 2.9.1 Quality control

Qualified acupuncturists, doctors, researchers, and statisticians in the First Teaching Hospital of Tianjin University of Traditional Chinese Medicine monitored and revised this experimental scheme. They also execute process quality control and data quality control, including compliance control implemented by the researcher, subject compliance control, and follow-up information integrity control, as well as creating a quality control team. Data quality control includes the composition of data supervisors, responsibilities and workflow, input process, interim analysis plan, research termination standard, data verification, data cleaning, etc. In addition, there will be regular supervision by clinical experts. Upon completion of the study, we will provide repository information for our data, all data underlying the findings will be made available as part of the manuscript or supporting information, or deposited in a public repository where the data will be recorded.

## 3 Discussion

Although several animal tests on PSD in existing studies focus on the pathogenesis of PSD, there is limited clinical evidence [25]. It is challenging to diagnose and assess PSD prior to clinical treatment. According to studies, only 5% of stroke survivors are diagnosed and treated for depression in routine clinical practice, as they frequently suffer cognitive and communicative impairments [26–28]. The difficulty of treatment is increased especially because of late diagnosis and screening, resulting in a relatively high proportion of small sample sizes and low-quality research in most clinical studies. The general lack of clinical evidence in the international field is also a massive problem in the future [21, 29].

Multiple biological and social psychological factors impact the pathogenesis of PSD, and its therapeutic mechanism has been intensively studied. There are studies discussing promoting neuroplasticity [30] and the perspective of central or peripheral immune inflammation [31]. Recent studies [3, 32] demonstrated that pro-inflammatory and anti-inflammatory mediators and the Sirt1/ NF-κB pathway are all implicated in the M1/M2 polarization of microglia in ischemic brain tissue. We previously discovered that "NRBP1", "SIRT1", "BDNF", "MAPK3", "CREB1" and key biological pathways such as NF-B, PI3K/AKT activation, and MAPK are critical for the incidence and development of PSD biomarkers [20]. Among them, SIRT1 can reduce the binding of NF-κB to inflammatory nuclear genes through the deacetylation of RelA/P65, a subunit of NF-κB, thereby reducing the production of inflammatory cytokines such as TNF-α and IL-1β. In the following animal experiments, we hypothesized that acupuncture might improve the inflammatory environment of PSD and regulate the polarization direction of M1/M2 microglia, and found experimentally and clinically that the expression levels of plasma SIRT1 (P value < = 0.05) and P65 (P value < = 0.05) were significantly lower after acupuncture treatment than in disease controls. Acupuncture treatment down-regulated the Sirt1/NF-κB pathway to inhibit the inflammatory responses, initially confirmed the intervention of acupuncture on these key pathways and targets, and to a certain extent, the mechanism by which acupuncture action promotes anti-inflammatory factor levels and neuronal protective regeneration, and thus improves PSD symptoms.

In this investigation, the antidepressants used for the control group are selective 5-hydroxytryptamine reuptake inhibitors (SSRIs), which have been shown to lower the risk of depression but may also raise the risk of fractures, seizures, brain hemorrhage, and gastrointestinal symptoms [9, 33]. The acupoints selected for the experimental group in this study are particular acupuncture points (Baihui(GV20), Yintang(EX-HN3), Fengfu(GV16), auricular concha, i.e., ear acupuncture acupoints Xin(CO15) and acupoints Shen(CO10)) in addition to the XNKQ acupuncture method of electro-acupuncture connection. Recent studies by Cai W et al [13] have indicated that electro-acupuncture (EA) appears to be an effective and safe therapy for PSD, with EA reducing depressive symptoms and improving neurological function. Several RCTs have proven the clinical efficacy of (electro)acupuncture in Baihui (GV20) and Yintang (EX-HN3) [34–38]. This is in close relation to the activation of the prefrontal lobes of the brain, which has been proven. In particular, Zhang, Z, J et al demonstrated that the use of an integrative acupuncture approach (electroacupuncture stimulation with body acupuncture) for the treatment of PSD, especially electrostimulation, reduced PSD and cognitive dysfunction [39, 40]. Fengfu (GV16) acupoint is located near the high cervical spine on the back and improves the blood supply of the vertebral artery. Several animal research and clinical data in recent years have demonstrated the effect of percutaneous vagal nerve stimulation on depression and even severe depression for the selection of auricular acupoints [3, 41, 42]. Among them, Wang, J. Y et al used the auricular concha region for stimulation and found an α7nAchR/NF-κB pathway associated with its antidepressant effect. These several pieces of high-quality evidence illustrate the importance of treatment of the auricular region for depression.

Both non-invasive and invasive auricular therapy have been shown to be effective and safe in two RCTs [12, 38]. In a meta-analysis, auricular acupuncture was also considered one of the safe treatments for non-drug interventions to improve PSD symptoms [29]. In the current study, many Meta-analyses of acupuncture combined with drugs for PSD suggest the potential advantages of acupuncture combined with drugs [43–45]. In an umbrella review, acupuncture and electroacupuncture plus conventional treatment with escitalopram, citalopram, sertraline, and fluoxetine showed no severe adverse events in patients with PSD [46]. Adverse reactions and side effects are likely to be mild, and several systematic reviews suggest that acupuncture and electroacupuncture treatments are either somewhat more effective than antidepressants or not significantly different from them, with fewer adverse events and side effects and a higher safety profile [47–49]. At the same time, it is also mentioned that low-quality studies account for a significant proportion, and that multicenter and large-sample double- or multi-blind randomized controlled clinical trials are still urgently needed.

In this trial, while assessing the clinical efficacy of acupuncture and electroacupuncture in the treatment of PSD, the effect of acupuncture on inflammatory factors in patients with PSD will be observed, and the mechanism of action will be further explored in depth to provide a theoretical and clinical basis for clinical acupuncture treatment of PSD. This study will observe multiple indicators as secondary outcomes that may have implications for enriching the theoretical and clinical evaluation of PSD diagnosis and treatment, leading to a more effective and multilevel exploration of the close association between acupuncture for PSD and mechanisms such as anti-inflammatory effects.

There are several limitations to this study. It is a single-center study, and the regional restriction of patients brings bias into the experimental research. Additionally, due to the limit of the trial date period, long-term patient follow-up is not achievable. However, we will remain committed to stepping up our efforts to standardize the treatment of PSD patients, to work to reduce negative effects and biases in the research process, and to provide high-quality evidence for future research in the acupuncture treatment of the PSD patient population as part of an integrative and complementary alternative medicine program for the treatment of PSD in the medical field.

## Abbreviations

PSD: post-stroke depression
XNKQ: xingnaokaiqiao (an acupuncture treatment)
DSM- Ⅳ/V: Diagnostic and Statistical Manual of Mental Disorders
HAMD-17: Hamilton Depression Rating Scale
SDS: Self-rating depression scale
NIHSS: The National Institute of Health stroke scale
MBI: Modified Barthel Index
TCM: Traditional Chinese Medicine
CRF: case report forms
RCT: randomized controlled trial
EA: electro-acupuncture
